### Secondary outcomes

#### Distress thermometer (weekly) [44]

The DT is a single-item measure of distress on a scale from 0 (no distress) to 10 (extreme distress). It has been validated as a worldwide measure of distress in people affected by cancer [45].

#### Comprehensive assessment of Acceptance and Commitment Therapy processes (weekly) [46]

The CompACT is a measure of the postulated mechanism of action and process of ACT. It consists of 23 items grouped into three sub-scales (openness to experience, behavioural awareness and valued action) which map closely onto our three core intervention sessions (modules C, D and E). Items are scored on a 7-point Likert scale, ranging from 0 (strongly disagree) to 6 (strongly agree). Psychometric properties of the CompACT have been shown to be adequate [46].

#### Brief Acceptance Measure (daily) [47]

The BAM is a three-item measure of psychological flexibility, specifically designed for use in single-case experimental designs and similar daily diary studies. Participants rate the previous 24 h on each of three dimensions of openness, awareness and engagement in valued activities on a 1 to 10 numeric scale. Scales are anchored at either end with indicative statements (e.g. 1 = struggling with thoughts, feelings and physical sensations versus 10 = open to thoughts, feelings and physical sensations). The BAM total score has an alpha of .71 and correlates strongly with the CompACT (*r = .*57, *p* < .001). The BAM is also sensitive to brief interventions designed to increase psychological flexibility in healthy adults.

#### Single-item QoL (daily)

A single quality of life item will be used to measure overall health. This is an item in which participants rate their health on a scale from 0 (worst imaginable health state) to 100 (best imaginable health state).

#### Feasibility outcomes

Although this study is not designed as a phase II feasibility study, relevant data will be collected on the number of patients screened for eligibility, number patients potentially eligible, number of patients recruited, and percentages of consented participants who complete the intervention and follow-up. Percentage drop-out, deaths during the study, and missing data (i.e. how much of the self-report questionnaires were completed by participants) will be monitored and recorded throughout the study. This information, together with the pilot acceptability data, will be used to inform the next phase of our research—a full feasibility study—by clarifying whether this is a potentially appropriate setting and timepoint in the patient pathway to deliver a psychological intervention. Undertaking full feasibility testing at this stage is inappropriate given that we do not yet have fully developed, acceptable, intervention content.

### Sample size

Potentially high rates of attrition need to be considered in any palliative care research when determining the sample size [51]. We aim to recruit 14 patients who complete the full intervention. Given a high probability of attrition, we expect to recruit approximately 20 patients allowing for such attrition. This sample size is more than sufficient for a single-case research design [48, 49] which purposely recruits only small samples given their idiographic focus. All participants who complete the intervention will be invited to participate in the qualitative interview.

### Data analysis

#### Quantitative data

Analysis of daily diary data (BAM and QoL single-item) will include visual analysis, calculation of stability envelope, between-phase mean level change and the percentage non-overlapping data, as is standard to single-case methodology [48]. Advances in statistical analysis of single-case experimental design data now allow researchers to calculate *p* values and effect sizes from single-case data, and to aggregate these across single cases, using metanalytic methods [49]; such analyses will be undertaken where data permit their use. These data will provide tentative and preliminary indications of effectiveness and will be reported with 95% confidence intervals where relevant. Weekly questionnaire data will be analysed with visual analysis and level change [50].

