### Participants: eligibility criteria and referral into the study

People over 16 years of age who have been told that they have an incurable cancer diagnosis and who are referred to specialist hospice day or community services at two hospice sites (one in England and one in Scotland) will be identified by hospice-based community nursing teams and invited to participate (see Table 2). Eligible participants must have a life expectancy of 4 months or more and, although limited to those affected by cancer, are not restricted to any particular cancer type. Seven to ten participants will be recruited from each recruitment site with the aim of completing the intervention with fourteen participants in total.

**Table 2 Tab2:** Protocol for recruitment and intervention delivery

1.	Identification of eligible participants by hospice team.
2.	Clinical teams to introduce study during routine visit to hospice/day service within 2 weeks of referral into service: information sheet provided and consent given to pass contact details to research team.
3.	Consent form returned to either clinical team or posted directly to research team. If returned to clinical team, to be posted to research team.
4.	Researcher has weekly contact with each clinical team and ensures maintenance of consent log each site. Maintains corresponding participant database.
5.	When consent form received by researcher, researcher makes contact with participant to: • Provide opportunity for further questions • Establish time frame for intervention delivery and • Arrange intervention sessions with psychotherapist for relevant site. Copy of consent form sent to clinical team to be placed in patient medical record.
6.	Researcher maintains log of sessions for therapist.
7.	Intervention session 1 (45–60 min) covering the assessment and engagement components, completion of baseline assessments, and preparing the participant to undertake the daily diary recordings. One week completion of baseline daily diary recordings.
8.	After 1 week completion of daily diaries (baseline), intervention session 2 (30–45 min) and completion of weekly questionnaires (15 min). Daily diary data collection continues.
9.	Intervention session 3 (30–45 min) and completion of weekly questionnaires (15 min). Daily diary data collection continues.
10.	Intervention session 4 (30–45 min) and completion of weekly questionnaires (15 min). Daily diary data collection continues.

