11.	Intervention session 5 (follow-up session) approximately 4 weeks later (30–45 min) and completion of weekly questionnaires (15 min). Information sheet and consent form given for interview. Daily diary data collection end with this session providing 9 weeks of data in total.
12.	Interview consent form received by research team. Copy provided to clinical team for patient medical record.
13.	Interview conducted by telephone 2 weeks after the end of the intervention (30 min).

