### Procedure

Ethical approval has been obtained from an NHS Research Ethics Committee (IRAS Project ID: 239683), in addition to relevant approvals from the research governance committees at Marie Curie Hospice Liverpool and Marie Curie Hospice Edinburgh. These two hospices have been selected pragmatically due to proximity to the collaborating University research sites; however, they afford a comparison between delivery across (a) two UK countries and (b) settings both with (Edinburgh) and without (Liverpool) a dedicated in-house hospice research lead.

Intervention sessions will take place at the hospice and last between 45 and 60 min. During the assessment interview, participants will complete baseline measures described below. These measures are repeated at the start of each subsequent intervention session. Daily process and QoL data will be gathered using either the smart-phone based app (Personal Analytics Companion (PACO) [40]) or a paper and pencil booklet equivalent. Completion of daily diaries will be monitored by the research team, and where three consecutive recordings are missed, the researcher will contact the participant by telephone to discuss barriers to completion. In the case of non-app-based diary data collection, we will not be able to undertake such regular checking (this can happen only at face-to-face meetings with the therapist for these participants), and thus, smartphone data collection methods will be strongly encouraged.

During the final intervention session, the therapist will explain the purpose of the follow-up qualitative interview, providing both written information and an opportunity to answer any questions that participants might have about this. Consent will be collected at that time by the therapist. Two weeks later, participants will be contacted by the researcher. Interviews will be conducted on a one-to-one basis either in the hospice (face-to-face) or via telephone. Interviews will be recorded for later transcription and analysis. The interview schedule is designed to help participants to express their experiences of taking part, acceptability of intervention content and perceived effectiveness of the intervention and its components. In addition, the interview will also ask about caregivers’ experiences during the intervention.

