#### Management of missing data

We assume that some participants will be unable to complete the weekly and daily self-report questionnaires at certain times during the study period. Given that the weekly questionnaires will be filled out immediately before each session and administered by the therapist, we anticipate no participants missing any weekly questionnaires. However, it is likely that participants will miss opportunities to record the daily measures. Members of the hospice team will be made aware if a participant misses three or more daily recordings in a row in order to determine if the reason is due to health deterioration prior to the research team following up with the participant directly to discuss any technical issues in recording this data.

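### The percentage of non-overlapping data rises mechanically when baseline diary days are missed, and neither named between-phase summary of the daily data adjusts for trend

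*Protocol article*

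**What the plan says.** The section Quantitative data states that analysis of the two daily measures (the BAM and the single quality-of-life item) "will include visual analysis, calculation of stability envelope, between-phase mean level change and the percentage non-overlapping data". The last two items are the only numerical comparisons between phases that the article names. A separate sentence covers p values, effect sizes and meta-analytic aggregation across cases; it cites a methods reference and adds that "such analyses will be undertaken where data permit their use". On interpretation: "These data will provide tentative and preliminary indications of effectiveness and will be reported with 95% confidence intervals where relevant".

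Table 2 sets the amount of data. The baseline is "One week completion of baseline daily diary recordings", hence at most 7 points, and the diary runs to the follow-up session, "providing 9 weeks of data in total", hence up to 56 days after baseline.

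On completeness, Management of missing data says that "it is likely that participants will miss opportunities to record the daily measures". Under Procedure, follow-up starts only "where three consecutive recordings are missed, the researcher will contact the participant by telephone", and for paper diaries: "In the case of non-app-based diary data collection, we will not be able to undertake such regular checking". Shorter or scattered gaps are therefore not chased, and gaps in a paper diary come to light only at a session.

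**The concern.** PND is the share of later days that exceed the best baseline day. It rests on one extreme value from a very short series. Removing a baseline day can lower that maximum or leave it unchanged, but never raise it. PND can therefore only rise or stay the same, whatever the reason the day was missed. A participant who filled in 3 baseline days would tend to show more apparent benefit than one who filled in 7, even if neither changed.

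The second weakness is shared with mean level change. Neither index has a trend term. These participants have incurable cancer, so daily ratings may drift over nine weeks for reasons unrelated to the sessions. A decline would hide benefit and an upward drift would mimic it.

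The article says that the primary aim of a single-case design is to attribute change to the intervention. Its Dissemination plan also expects that the data may be enough for professionals to decide whether to use the manual at once. The per-case summaries will feed that judgement.

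**Working it through.** The article gives no PND, SD, autocorrelation, drift or missing-day rate, so there is no stated figure to reproduce. From the article: at most 7 baseline days, up to 56 later days, missed days expected. Assumed: 3 to 7 completed baseline days; 14 or 56 later days; SD of 1; the drifts and autocorrelations below.

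**1. PND with no effect.** For independent continuous days, a given later day exceeds all nA baseline days with probability 1/(nA + 1).

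| Completed baseline days | Expected PND |
|---|---|
| 7 | 1/8 = 12.5% |
| 5 | 1/6 = 16.7% |
| 4 | 1/5 = 20.0% |
| 3 | 1/4 = 25.0% |

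With 56 later days, PND reaches 50% when the top 28 of all nA + 56 values are later days. The probability is C(nA + 28, nA)/C(nA + 56, nA): 1.2% for 7 baseline days, 7.4% for 4 and 13.8% for 3.

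Simulation of 20,000 first-order autoregressive series with 56 later days gives the same pattern. At autocorrelation 0.3, mean PND is 14.8% with 7 baseline days and 26.5% with 3; at 0.5 it is 17.6% and 28.2%. On an integer 1 to 10 scale (assumed mean 5.5, SD 2, autocorrelation 0.3) it is 10.6% and 20.5%.

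**2. Mean level change with days missed at random.** The expected value is 0.00 SD for 7, 5, 4 or 3 baseline days. Only precision falls: with 56 later independent days the sampling SD is √(1/7 + 1/56) = 0.40 with 7 baseline days and √(1/3 + 1/56) = 0.59 with 3. If bad days are the ones missed, the baseline mean is too high and the change looks smaller.

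**3. An all-pairs index.** NAP is the proportion of baseline-later pairs in which the later day is higher. In the same simulations its null mean is 0.50 with 7, 5, 4 or 3 baseline days, at autocorrelation 0, 0.3 and 0.5.

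**4. Trend.** Apparent level change = true step + drift × distance between phase midpoints.

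- 7 baseline days have midpoint 4. Days 8 to 21 have midpoint 14.5, a gap of 10.5 days (1.5 weeks). Days 8 to 63 have midpoint 35.5, a gap of 31.5 days (4.5 weeks).
- Decline of 0.2 SD per week, true step 0.40 SD: 0.40 − 0.2 × 1.5 = 0.10 SD over 14 later days; 0.40 − 0.2 × 4.5 = −0.50 SD over 56.
- Decline of 0.1 SD per week: 0.40 − 0.15 = 0.25 SD, and 0.40 − 0.45 = −0.05 SD.
- No effect, upward drift of 0.02 SD per day, 56 later days: 0.02 × 31.5 = 0.63 SD, with mean PND 27.9% (simulated, all 7 baseline days).

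**5. Would a model with a common time slope settle it?** Take 7 and 14 days, no decline, and a benefit that builds linearly to 0.6 SD at day 14 after baseline. Mean level change is 0.6 × 7.5/14 = 0.32 SD. The within-phase sums of squares of time are 7 × 48/12 = 28 and 14 × 195/12 = 227.5, so the common slope is (0.6/14) × 227.5/255.5 = 0.038 per day. The phase effect is 0.32 − 0.038 × 10.5 = −0.08 SD: the slope absorbs the benefit. The variance of the phase effect rises from 1/7 + 1/14 = 0.214 to 0.214 + 10.5²/255.5 = 0.646, so its standard error grows √(0.646/0.214) = 1.74-fold.

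**The case against.** The strongest defence is that PND and mean level change are not the whole plan. The same sentence lists visual analysis, in which trend can be seen, and a stability envelope, which shows baseline variability. The results are called tentative, the study is a modelling study, and a fuller analysis plan may say more. This stands as a limit on severity. It does not rescue PND, which the article names and whose dependence on baseline completeness no plot removes.

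A reader might go further in four ways that the article does not support.

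- That both indices look better when baseline days are missed. This holds for PND only (step 2).
- That p values and intervals will be wrong. A t-test treating days as independent, at a nominal 5%, would reject in about 13.5% of null series at autocorrelation 0.3 and 21.5% at 0.5. But the article names no such test, and whether the methods it cites allow for serial correlation cannot be seen here. This is a condition to state, not an error shown.
- That the two indices are the only source of effect sizes and p values. Those come from a separate, conditional sentence.
- That the words "such analyses will be undertaken where data permit their use" mean selecting the fitter participants. They condition the use of the analyses; selection is an inference.

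It is also fair to object to a multilevel model with a time slope as the required main analysis. The skills are taught module by module, so gradual benefit is plausible, and step 5 shows that such a model can erase it.

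**Conclusion.** The concern holds in a limited form. PND has a null value that doubles from 12.5% to 25% as completed baseline days fall from 7 to 3. The article expects missed days, so PND values are not comparable between participants. The exact figures assume independent continuous days; the rise persists under the autocorrelation and integer scoring tried. Mean level change does not share this fault when days are missed at random. Neither index separates an effect from a trend, and the size of that distortion depends entirely on the assumed drift: a true 0.40 SD step appears as 0.25 or 0.10 SD over 14 later days for declines of 0.1 or 0.2 SD per week. The documents do not show that planned p values or intervals are invalid, or that participants will be selected.

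**What to change.** In Quantitative data:

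- Replace PND as the per-case overlap index with NAP or Tau, whose null value does not depend on the number of baseline points.
- Show a baseline-trend-corrected version (Tau-U) as a sensitivity result. NAP and Tau are not themselves protected against trend.
- Print the number of completed baseline days beside every per-case estimate.
- Keep PND and mean level change as descriptive figures.
- State that any p value or 95% confidence interval from the daily data will allow for serial correlation between days.
- Optionally add a multilevel model with a time slope and first-order autoregressive errors, as a sensitivity analysis only.

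The cost is a few sentences and a little extra analysis; no additional data are needed. The figures may look less favourable, and a trend correction estimated from 7 or fewer baseline points will be imprecise, which should be said where it is reported.

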#### Management of missing data

We assume that some participants will be unable to complete the weekly and daily self-report questionnaires at certain times during the study period. Given that the weekly questionnaires will be filled out immediately before each session and administered by the therapist, we anticipate no participants missing any weekly questionnaires. However, it is likely that participants will miss opportunities to record the daily measures. Members of the hospice team will be made aware if a participant misses three or more daily recordings in a row in order to determine if the reason is due to health deterioration prior to the research team following up with the participant directly to discuss any technical issues in recording this data.

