In addition to local hospice induction, training will be provided by the intervention authors ([name] and DG) through the use of self-study materials, simulated video role-play, and practice role-play opportunities. The level of training provided will be tailored dependent on the prior experience and skills of the individuals appointed to this role. Before delivery of the intervention to study participants, therapists will undertake a competency assessment where their delivery of the intervention (with a simulated patient) will be video-recorded and assessed against a previously validated ACT rating scale [39]. Therapists are required to score at least 90 (corresponding to ‘average competence’) before delivering the intervention in the clinical setting. Where this level of competency is not achieved, further training will be provided. There will be one therapist at each clinical site to ensure continuity for participants recruited and consistency of delivery between participants for added methodological quality. Clinical supervision will be provided by an existing member of the team who is suitably qualified for this role ([name]).

Module A takes the majority of the first intervention session. Session two then covers module B plus one of the ACT-specific modules (C, D or E) in an order determined by the therapist to best meet the needs and priorities identified and negotiated with the participant in session one. Sessions 3 and 4 cover the remaining module content (C, D or E), with module F delivered at 1-month follow-up. The level of flexibility inherent in the design will allow for greater understanding of delivery differences between participants and a more refined understanding of which elements produce what kinds of changes in outcome and process variables.

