### Data collection

Weekly self-report questionnaires will be administered throughout the intervention to assess changes in quality of life (our primary outcome), distress (secondary outcome) and ACT intervention processes (as potential mediating variables).

Daily diaries will be used to attempt more sensitive and specific measurement of process change. Daily recordings are known to produce more valid and accurate results than retrospective summary reports [41]. Participants will have the choice to access these daily recordings either via a smartphone app or paper versions to ensure ease of access. The use of a smartphone app (PACO [40]) for daily data collection is relatively novel within palliative care trials, and so, this pilot data will allow us to conclude whether this is a feasible alternative to paper-based data collection methods for similar work.

Data will also be collected on the number of patients approached about the study, the number then recruited, attrition, and reasons for non-eligibility in order to inform later feasibility and effectiveness trials.

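### The treating therapist administers the weekly primary and secondary questionnaires, so any reporting effect that grows after baseline may pass as benefit

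*Protocol article*

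**What the plan says.** Under Management of missing data, the article states that the "weekly questionnaires will be filled out immediately before each session and administered by the therapist", and on that ground expects no missing weekly forms. The Procedure section places the first completion in the assessment interview and adds: "These measures are repeated at the start of each subsequent intervention session". Table 2, step 7, describes session 1 as "covering the assessment and engagement components, completion of baseline assessments, and preparing the participant to undertake the daily diary recordings". Steps 8 to 11 attach the weekly questionnaires to sessions 2, 3, 4 and 5.

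The administrator is the treating therapist, because under Intervention: rationale and development, "There will be one therapist at each clinical site to ensure continuity for participants recruited". The Data collection section says that the weekly forms serve "to assess changes in quality of life (our primary outcome), distress (secondary outcome) and ACT intervention processes (as potential mediating variables").

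The Quantitative data section plans visual inspection and level change for the weekly data. The daily measures (BAM and a single quality-of-life item) come by app or paper booklet, not through the therapist.

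**The concern.** A participant who fills in a form given out by the person treating them may shade the answers, out of courtesy or because they sense what is hoped for. The outcomes are self-reported and unblinded. The only comparison is between phases within a person, so no parallel group would show the same shading without the therapy.

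The Methods section says that a single-case design aims to show that observed change comes from the intervention. A reporting shift that appears after baseline would be read as such a change in the primary outcome. CompACT is exposed in a second way. Its subscales match the three core modules, and it is a candidate mediator. If the same shift acted on CompACT and FACIT-Pal, the two would move together and could look like mechanism.

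The results will be used. The Manual revision section feeds the quantitative data into the revised manual, and the Dissemination plan expects that the data may let professionals decide whether to adopt it straight away.

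**Working it through.** The plan gives no figure for this point, so there is none to reproduce. The check asks which kinds of reporting shift survive the planned contrast.

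**Inputs**
- Weekly occasions: sessions 1, 2, 3, 4 and 5 (Procedure; Table 2, steps 7 to 11). All 5 of 5 are tied to a session with the therapist.
- Phase split: sessions 1 and 2 as baseline, because the forms at session 2 are completed at its start, after the one-week diary baseline; sessions 3, 4 and 5 as post-baseline. The article does not spell out this split for the weekly data; it is my reading of Table 2.
- Reporting shift s at each occasion, in scale points. The values below are assumptions chosen to show the mechanism, not estimates.

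**Formula**

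Bias in level change = mean(s3, s4, s5) − mean(s1, s2).

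Let a be a shift present at every occasion and d an extra shift that begins later.

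| Pattern | Calculation | Bias |
|---|---|---|
| Constant: a = 5, d = 0 | 5 − 5 | 0 |
| Extra from session 3: a = 0, d = 2 | 2 − 0 | 2 |
| Extra from session 3: a = 0, d = 5 | 5 − 0 | 5 |
| Extra from session 3: a = 5, d = 5 | 10 − 5 | 5 |
| Extra already from session 2: a = 0, d = 5 | 5 − (0 + 5)/2 | 2.5 |

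**Reading**
1. A constant shift drops out, whatever its size.
2. A shift that begins after baseline passes through one for one, whatever the value of a.
3. A shift that has already begun by session 2 is partly absorbed into baseline, so half of it remains.
4. The documents give no value for d, so the bias cannot be computed.

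**Is a growing shift plausible?** Table 1 makes warmth and engagement part of module A, which takes up most of session 1, so the relationship is built up on purpose from the first meeting. The last forms accompany the session in which progress is reviewed and contact ends. That makes growth plausible. It does not show that growth occurs.

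**How far do the daily data help?** The daily quality-of-life item rates overall health from 0 to 100, not the FACIT-Pal domains. No daily distress measure is described. BAM covers openness, awareness and engagement, so it is a nearer counterpart to CompACT. Completion of paper booklets can be checked only at meetings with the therapist. The cross-check is partial.

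**The case against.** The strongest reply is that baseline is collected in the same way by the same therapist, so the setting is held constant and its effect cancels. That stands for any constant effect, and it limits the point to the part that grows.

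A reader might infer that the first ratings predate any relationship, so that the bias cannot cancel. The documents do not support this. The first forms are completed within session 1, at an unstated moment, and the second set follows a full engagement session. A reader might also infer that CompACT is rated straight after its skills are taught. It is not: forms come before each session, and the last set follows about 4 weeks without one.

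Therapist administration also has a stated purpose, complete weekly data, in a population where the Sample size section expects high attrition. That is a real benefit, and any change should preserve it.

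The article may leave private completion, or who sees the answers, to the full protocol. That is fair, and to be administered by the therapist need not mean that the therapist reads the answers. But therapist administration is itself stated, and it is what the point rests on.

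Finally, this is a phase I modelling study that calls its effectiveness findings tentative, and the researcher's later interview gives another view of perceived benefit. This lowers the stakes without removing them, given the planned uses of the data. Sealed forms would not remove all demand effects either, since participants still know that they are rating a therapy they receive.

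**Conclusion.** The point holds as a risk of bias, not as a demonstrated bias. The treating therapist administers the primary outcome, the distress thermometer and CompACT at all five occasions, and the planned within-person contrast cannot separate a growing reporting effect from benefit. If such an effect exists and begins after baseline, it enters the level change in full. If it is constant, it contributes nothing.

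Its direction and size are unknown. Improvement is the direction to worry about, because courtesy towards a therapist would tend that way, but the documents do not establish it. A reader might be tempted to put a figure on it. FACIT-Pal has 7 + 7 + 6 + 7 + 19 = 46 items, so an assumed shift of 0.1 to 0.2 points on every item would give 46 × 0.1 = 4.6 to 46 × 0.2 = 9.2 points. Nothing in the documents supports that per-item shift, or its applying equally to physical and emotional items, so it should not be quoted as the size of the problem.

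The conclusion assumes the phase split described above and that no safeguard exists beyond the article. The change is worth making because it reduces an avoidable risk to the primary outcome at little cost.

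**What to change.** Amend Management of missing data and Procedure, with the matching steps of Table 2, as follows:

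- Participants still complete the weekly forms on site immediately before each session, which keeps the reason given for expecting complete data.
- They do so privately, and return the forms to the research team in a sealed envelope or through the app already used for the diaries.
- Anyone who needs help gets it from existing staff other than the therapist.
- Session 1 follows the same procedure, so that baseline and later occasions stay comparable.
- The report shows the weekly results beside the daily quality-of-life item as a consistency check, noting that the two measure different things.

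The cost is envelopes or an extra app form, slightly more handling, and no added assessor. There is a small risk of incomplete forms in frail participants, and the therapist loses sight of the research scores during the session. Existing arrangements for responding to distress should be unaffected.
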